#### 3.2.12. Enjoyment (Physical Activity Enjoyment Scale-8 (PACES-8)

A shortened version of the physical activity enjoyment scale (PACES-8) will be administered by the trial AEP at the conclusion of the supervised training sessions at 4-weeks, 8-weeks, and 12-weeks to assess participant enjoyment. This is a simplified version of the physical activity enjoyment scale, as originally described by Kendzierski and DeCarlo [103], with strong psychometric integrity, and it has been validated in older populations [104]. The PACES-8 consists of 8 subscales that each relate to an aspect of enjoyment. Along a 7-point continuum for each subscale, participants are asked to provide a rating to reflect their agreement with one of two bi-polar statements at each end of the continuum (e.g., It’s no fun at all, It’s a lot of fun). The PACES-8 has been shown to have good internal reliability coefficients at two timepoints six months apart (McDonald’s ω = 0.93, 0.93) [104] and correlated positively with experienced physical change (r = 0.42, 0.47), psychological/emotional change (0.41, 0.42), and functional change (0.39, 0.29) at timepoints 1 and 2, respectively.

### 3.3. Tertiary Outcomes

#### 3.3.1. Qualitative Analysis

To gain an in-depth understanding of the experiences of participants and the perceived benefits and barriers of the intervention, semi-structured interviews will be conducted. An interviewer will conduct 45 min face-to-face interviews with participants after the completion of the 3-month unsupervised exercise intervention. A standard script will be used. Interviews will be transcribed and analyzed in NVivo 12 Plus (QSR International, Chadstone, Australia) using the constant comparison coding method to reduce the data to themes using a qualitative descriptive approach. Codes will be assigned to salient text segments across the entire data set, then combined to define overarching themes. Two researchers will develop a descriptive coding frame based on *a priori* concepts and will work collaboratively to refine the coding frame and develop concordance about the scope and content of each code. This coding frame will provide a “start list” to which inductive codes will be added to capture emergent concepts during this and the subsequent coding process [105].

Initial themes will be developed by reading within and across the codes to look for conceptual patterns and by synthesizing the points that are most relevant to the research questions [105]. Themes will be further refined through this reflective process, with review of the transcripts and audio recordings to check the validity of assertions. Throughout this process, analysis will involve reviewing data against each other to identify conceptual differences/similarities and degrees of prevalence and strength.

#### 3.3.2. Feasibility and Adherence

The feasibility of the program will be measured by the rates of eligibility, recruitment, attrition, attendance (defined as: n _sessions attended_ × n _sessions prescribed_^−1^ × 100), and adherence to the program intensity and duration for each component of the intervention, i.e., aerobic, resistance and bone loading.

Attendance at the supervised sessions will be recorded by the supervising AEP, in addition to the self-reported completion of the weekly home-based session. Adherence records will be completed by the supervising AEP at each supervised session with detailed reasons for non-adherence recorded. Adherence to the aerobic component of the protocol will be defined as: minutes at the workload prescribed by the AEP, i.e., 12 min at moderate-to-vigorous intensity (60–85% HR_peak_) and 8 min at high intensity (>85% HR_peak_). Adherence to the resistance training component of the protocol will be defined as: minimum of 80 repetitions (5 exercises, 2 sets, 8 repetitions = 5 × 2 × 8) at a minimum intensity of 5/10 on the OMNI-RES scale [44]. Adherence to the bone loading component of the protocol will be defined as: minimum of 80 repetitions. The minimum intensity for adherence will be 2, where 1: isometric exercise targeting spine and/pelvis; 2: marching; 3: stomping; 4: jumping; 5: drop jump from height (range 10–30 cm). Unilateral exercises, i.e., marching, stomping, will have a minimum of 80 impacts per leg (4 × 20 impacts per leg), with a minimum of 80 total impacts for bilateral exercises, i.e., jumping, drop jumping from height.

*A**priori* cut points were defined to determine successful adherence to each component of the exercise program. Cut-off values for the feasibility criterion (a recruitment rate of ≥25% [106]; an attrition rate of <25% [107]; and attendance and adherence of ≥75% [108]) were established *a priori* as clinically relevant based on previous studies in other cancers.

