Bone loading activities will progressively increase across the intervention from 40 impacts per session to 100 impacts per session for non-affected skeletal sites [45]. Participants with pelvic, axial skeleton (lumbar), or lower limb bone lesions will be prescribed isometric exercise targeting the spine and pelvis in positions of support, e.g., supine, prone, or seated for unstable lesions. For participants without the aforementioned bone lesions, the intensity of impacts, based on the ground reaction forces produced, will be progressively increased across the intervention, i.e., level 1: isometric exercise targeting spine and/or pelvis; 2: marching; 3: stomping; 4: jumping; 5: drop jump from height (range 10–30 cm) [45]. Progression will account for any pre-existing musculoskeletal injuries and/or pain. Participants will be instructed to land on their heels with approximately 5° knee flexion on impact. One minute rest periods will separate jump sets with a minimum of four sets of 20 impacts per set. Unilateral exercises, i.e., marching, stomping, will have a minimum of 80 impacts per leg (4 × 20 impacts per leg), with a minimum of 80 total impacts for bilateral exercises, i.e., jumping, drop from height.

Exercise sessions will be cancelled/postponed if the participant experiences a fever (>38.0 °C), infection, platelet count <50 × 10^9^/L, hemoglobin <90 g/L, higher grade cardiac arrhythmias, or life-threatening clinical complication. Neutropenia of any grade without fever will not be considered a contraindication to exercise training.

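### The bone-loading adherence rule requires level 2 or above, so participants prescribed level-1 isometric work because of bone lesions score as non-adherent when they comply

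*Protocol article*

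**What the plan says.** Section 3.3.2 (Feasibility and Adherence) sets out to measure "adherence to the program intensity and duration for each component of the intervention, i.e., aerobic, resistance and bone loading". For bone loading it gives a volume floor, "Adherence to the bone loading component of the protocol will be defined as: minimum of 80 repetitions", and an intensity floor, "The minimum intensity for adherence will be 2, where 1: isometric exercise targeting spine and/pelvis", with marching as level 2. No separate rule is given for participants who are restricted because of lesions. Reasons are kept for sessions that fall short ("with detailed reasons for non-adherence recorded"), but nothing says that a recorded reason changes the score. The feasibility cut-off is stated once, as "attendance and adherence of ≥75" per cent, after a sentence saying that cut points define success for each exercise component.

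Section 2.5 (Exercise Intervention) fixes the prescription. "Participants with pelvic, axial skeleton (lumbar), or lower limb bone lesions will be prescribed isometric exercise targeting the spine and pelvis", and the sentence goes on "in positions of support, e.g., supine, prone, or seated for unstable lesions". For participants without those lesions, impact intensity "will be progressively increased across the intervention, i.e., level 1: isometric exercise targeting spine and/or pelvis; 2: marching", and so on up to drop jumps. The same section gives a ramp from 40 to 100 impacts per session for unaffected sites, and also a minimum of four sets of 20.

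**The concern.** One section prescribes an activity and the other rules that the activity cannot count. A lesion-restricted participant who completes every prescribed bone-loading session scores zero on that component, and could score otherwise only by doing impact work that section 2.5 does not prescribe for them.

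The figure then mixes two different things: what was prescribed and what participants did. A low value could mean that patients did not manage the program, or that they followed a safety restriction faithfully. The distinction matters here because the introduction presents exercising with bone lesions as a major safety worry for hematologists and patients, and feasibility is one of the questions the trial means to answer. What is at stake is a tertiary feasibility result and whether it passes its cut-off.

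**Working it through.** There is no planned figure to reproduce. The check compares two definitions and then works out the consequence.

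**Step 1: is the prescribed activity below the floor?** Section 2.5 prescribes isometric exercise of the spine and pelvis to the lesion group. Sections 2.5 and 3.3.2 both define level 1 as isometric exercise of the spine or pelvis. Section 3.3.2 puts the floor at level 2. The prescribed activity is therefore below the floor.

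**Step 2: does the qualifier on unstable lesions remove the conflict?** It may attach to the seated position, to the supported positions, or to the whole prescription. On the narrowest reading only participants with unstable lesions are prescribed level 1. They still fail the rule. The qualifier changes how many are affected, not whether any are.

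**Step 3: do the other components behave this way?** No. The aerobic rule counts minutes at the workload the exercise physiologist prescribed. The resistance floor is 5 out of 10 on the OMNI-RES scale, below the prescribed 6–9. Only the bone-loading intensity floor lies above a level that the protocol itself prescribes.

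**Step 4: size.** Let p be the share of bone-loading sessions prescribed at level 1 because of lesions, and a the adherence in all other sessions. Neither is given, so both are assumptions. Assume also that level-1 sessions stay in the denominator and score 0, and that sessions are pooled. Then

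reported adherence = (1 − p) × a

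| p | a = 100% | a = 90% | a = 80% |
|---|---|---|---|
| 10% | 90% | 81% | 72% |
| 20% | 80% | 72% | 64% |
| 25% | 75% | 67.5% | 60% |
| 30% | 70% | 63% | 56% |

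The 75% cut-off is missed once p exceeds 1 − 0.75/a:
- a = 100%: 1 − 0.75 = 25%
- a = 90%: 1 − 0.75/0.90 = 16.7%
- a = 80%: 1 − 0.75/0.80 = 6.25%

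In head counts, 60 participants randomized 1:1 gives 30 in the exercise arm. Take full compliance, equal sessions, and affected participants at level 1 throughout. With 7 affected the figure is 23/30 = 76.7%, which passes. With 8 affected it is 22/30 = 73.3%, which fails.

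If sessions were scored against the prescription, full compliance would give 100% whatever p is.

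**Step 5: the volume floor.** The ramp in section 2.5 starts at 40 impacts, half of the 80 that section 3.3.2 requires. If the ramp governs, early sessions done as prescribed fail on volume too. If the stated minimum of 4 × 20 = 80 governs, they do not. The article does not say which, so no size is attached to this part.

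**The case against.** The strongest defence is that a fixed floor is a legitimate choice. The component is meant to deliver impacts, and a level-2 floor shows whether impact loading was feasible in myeloma. The resistance rule is also a fixed minimum. Scoring against the prescription would let the exercise physiologist raise adherence simply by prescribing less. This stands as a reason to keep the fixed-dose figure. It does not justify calling that figure adherence to the program, because section 2.5 individualizes the program by lesion location and extent.

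A second defence is that the article does not state the denominator. Restricted participants might be treated as not applicable, and the full protocol and case report form are not shown. This also stands in part. If level-1 sessions were excluded, the bias would disappear, so the size is conditional on their being kept. As printed, though, the rule has no exemption.

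A third is that recorded reasons would let the affected sessions be found and reported apart. That is true, but the headline figure would not change.

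A reader might infer more than the documents support:
- That p is near the introduction's figure of up to 85% with lytic lesions. That figure covers any site over the whole disease course, and entry requires medical clearance, so it is not an estimate of p.
- That compliant participants fall below the 70% adherence cut-point in section 5. That section does not say which adherence measure it uses, and no rule for combining components is given.
- That lesion-free participants are generally penalized. Level 1 is the lowest step for them, but the text does not say that everyone starts there or for how long.

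**Conclusion.** The conflict is real and lies between two stated rules. Participants prescribed isometric work because of lesions are scored non-adherent for complying, and the bone-loading adherence figure is biased downward whenever such sessions occur and remain in the denominator. With full compliance the figure equals 1 − p and misses the 75% cut-off once p exceeds 25%, or at a lower p if adherence elsewhere is imperfect. Applying the cut-off to bone loading alone follows the wording about each component but is not stated outright. The actual size is unknown, because p is not given and the reach of the lesion wording is ambiguous. The 80-repetition floor adds a similar conflict only if the 40-to-100 ramp governs.

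The consequence is confined to a tertiary feasibility measure. The documents tie it to no stopping rule, and they give no ground for inferring an effect on the primary quality-of-life comparison. It is worth correcting because the correction is cheap and loses no information.

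**What to change.** In section 3.3.2, define a bone-loading session as adherent when the participant completes the level and volume that the exercise physiologist prescribed in advance for that session. Level 1 then counts where isometric work is prescribed because of lesions, and a session prescribed fewer than 80 impacts under the ramp is judged on its own target. Apply the 75% cut-off to this figure.

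Report separately, as impact dose delivered, the share of sessions at level 2 or above with at least 80 impacts, together with the number of participants restricted to isometric work. This keeps the information in the present rule and makes repeated down-prescription visible.

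The cost is small. The prescribed level and volume must be recorded before each session, and the adherence figure alone no longer shows the absolute dose, which the separate report supplies.

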#### 3.3.3. Adverse and Serious Adverse Events

Safety of the intervention will be measured through reporting adverse and serious adverse events. The trial AEP will record at each testing and supervised training session whether an adverse event has occurred and, if so, the AEP will provide details to the governing ethics committee. Events at unsupervised sessions will require self-report by the participant to the trial AEP. Adverse events will be reported to the study clinicians and the participant’s treating doctor for further decisions on safety and any required investigations. Trial insurance provided through the sponsor, The University of Queensland, includes provision for post-trial care if required.

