### 2.1. Trial Design and Setting

The study design is depicted in Figure 1. People diagnosed with MM will be invited to participate in this multi-site, single blind, randomized waitlist-controlled trial. A waitlist control group design was chosen to reduce participant dropout from a non-exercise control group [39]. Participants randomized to the waitlist control group will be encouraged to maintain their customary physical activity during the 3-month wait period.

The exercise program follows a stepped down supervisory approach with reduced supervision after three months. All participants will complete an assessment battery (see Table 1) at baseline, at the end of the supervised phase, and at 6- and 12-months following baseline testing (see Figure 1).

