### 2.4. Randomization

Following completion of the baseline testing session, participants will be stratified by disease stage (active treatment, transplant eligible; active treatment, transplant non-eligible; non-active; relapsed) before being randomly assigned (1:1 allocation ratio) to waitlist control (WT) or exercise intervention (EX) group. A research officer independent of the study will perform the randomization using a computerized random number generator. To ensure allocation concealment, a block size of four will be used. Randomization history will be kept secure by the independent research officer in an electronic password-protected file. The allocation result will be communicated in confidence by the independent research officer to the trial’s accredited exercise physiologist (AEP) within 48 h after completing the baseline testing session. The principal investigator will conduct all testing sessions and analyses and be blinded to group allocation. Un-blinding will not be permissible under any circumstances. Due to the nature of the study, neither the AEPs prescribing the training nor participants can be blinded to the randomization assignment.

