## 3. Outcome Measures

The data and sample collection schedule is depicted in Figure 1, and detailed in Table 1. All testing sessions will be conducted in the research laboratories within the School of Human Movement and Nutrition Sciences at The University of Queensland and will be completed by two researchers, consistently assigned to the same tasks. Prior to each testing session, participants will be asked to: (i) maintain a hydrated state in the 24 h prior to testing; (ii) fast, including abstaining from caffeine and alcohol intake for 8 h prior to testing; and (iii) avoid any vigorous, high or unaccustomed moderate intensity physical activity for the preceding 24 h. Wherever possible, the testing session will be scheduled for the morning hours, with all subsequent testing timepoints scheduled at the same time of day for each participant. Prior to the baseline testing session, participants will be required to record a 3-day diet diary, which they will be required to replicate prior to all subsequent testing sessions. Participant adherence to the testing standardization measures will be evaluated prior to the commencement of each assessment. If testing standardization measures are not met, the researcher will confirm the participant’s understanding of the pre-testing requirements and reschedule the assessment for another day. Inter- and intra-tester reliability will be determined for data-collecting investigators for all outcome measures as appropriate. Assessments will be performed in a consistent order with appropriate rest periods to minimize testing fatigue. Any alterations in medical status or medications, hospital admission, or concomitant study participation will be documented for future reference during analysis of results.

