Throughout the V̇O_2peak_ test, HR, blood pressure, and RPE (6–20 Borg scale) will be monitored. Blood pressure will be monitored every two minutes, whilst HR will be continuously monitored throughout the V̇O_2peak_ test using the COSMED automatic blood pressure cuff. Participants’ RPE will be recorded in the final 20 s of each minute. The test will be terminated when participants reach volitional fatigue, when participants choose to terminate exercise, or at the discretion of the researchers, in accordance with the indications for exercise test termination as outlined by the ACSM [40]. HR recovery will be monitored for 5 min immediately following the V̇O_2peak_ test, with participants only discharged from the laboratory once their blood pressure and HR return to within 10–15 mmHg and 15 bpm of pre-exercising levels.

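### The unblinded exercise physiologist records adverse events at testing sessions, so the assessor blind is not protected at post-baseline tests

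*Protocol article*

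**What the plan says.** Section 2.1 describes a "multi-site, single blind, randomized waitlist-controlled trial" design. Section 2.4 identifies who is blinded: "The principal investigator will conduct all testing sessions and analyses and be blinded to group allocation". It rules out any exception: "Un-blinding will not be permissible under any circumstances". It also says who is not blinded: "neither the AEPs prescribing the training nor participants can be blinded to the randomization assignment". On timing, "The allocation result will be communicated in confidence by the independent research officer" to the trial AEP, within 48 h after the baseline testing session.

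Section 3.3.3 then sets out how safety data are collected: "The trial AEP will record at each testing and supervised training session whether an adverse event has occurred". Events at unsupervised sessions reach the same AEP by participant self-report.

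Section 3 describes the staffing of the tests differently from Section 2.4. It says that testing "will be completed by two researchers, consistently assigned to the same tasks". Only the principal investigator is stated to be blinded.

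**The concern.** At each test after baseline, a person who knows the participant's arm has a duty at the session run by the assessor who must not know it. By the 3-month test, exercise participants have been offered 24 supervised sessions with an AEP, while waitlist participants have had none. Visible familiarity, or an event query that touches on training, could tell the assessor the arm without anyone intending it.

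What is at stake is a specific group of secondary outcomes. Because the quality-of-life result comes from participants who know their allocation, readers will look to the physical tests for corroboration, and the assessor blind is what makes those tests more credible. Several depend on maximal effort and so on how the tester encourages the participant. The exercise test may also be ended "or at the discretion of the researchers". An assessor who has guessed the arm could influence effort, plausibly in favour of exercise.

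**Working it through.** No calculation bears on whether the sections conflict, so the check sets them side by side.

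1. **Who must be blind.** Section 2.4: the principal investigator, as tester and analyst, with unblinding never allowed.
2. **Who knows the arm, and from when.** Section 2.4: the trial AEP, within 48 h after baseline testing. The AEP therefore knows the arm before every later test.
3. **Who has a task at the tests.** Section 2.4 gives the testing to the principal investigator, Section 3 to two researchers with fixed tasks, and Section 3.3.3 gives event recording to the AEP.
4. **Any separation between 2 and 3.** None is stated. Section 3.3.3 does not say when the AEP asks, where, or whether the tester sees the answers.
5. **Which visits are exposed.** Baseline testing is completed before randomization, so it is not. In Table 1 the exposed visits are those at 3, 6 and 12 months, plus the waitlist arm's repeat of the baseline battery after three months of usual care (footnote a). The 3-month comparison matters most, because it is the only one against a group that has not yet begun the programme.
6. **How many participants.** The ceiling at 3 months is the 60 recruited. With the 25% dropout anticipated in Section 5, 60 × (1 − 0.25) = 45 would attend. These are numbers of tests exposed, not numbers of tests biased.
7. **Which outcomes.**
   - *Exposed:* the cardiopulmonary test (3.2.1) and grip, 30 s sit-to-stand, mid-thigh pull and Y-balance (3.2.4). A tester runs all of them, and they depend on effort.
   - *Largely outside:* DXA and pQCT scans, blood markers, accelerometry and the questionnaires, which depend far less on the tester.
   - *Not affected:* the primary outcome, the QLQ-C30 summary score, which unblinded participants complete themselves.

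Steps 1 to 4 show a stated rule that works against a stated blind. Steps 5 to 7 limit where it can do harm.

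**The case against.** The strongest reply is that an unblinded recorder does not by itself unblind the tester. Section 3.3.3 does not put the AEP in the room during measurement, does not have the AEP score any outcome, and does not have the AEP discuss training with the tester. If events were recorded separately, the blind could hold. That stands. A reader might infer that the blind cannot hold at all, but the text supports only the weaker statement that nothing in it protects the blind.

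Other limits also stand:

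- **Ending the exercise test.** The discretion to stop is tied in the same sentence to the ACSM indications for termination. Section 3.2.1 also includes the oxygen uptake efficiency slope, which it describes as unaffected by whether exercise is submaximal or maximal. This narrows the room for bias in the cardiopulmonary test but does not remove it, because the test otherwise runs to volitional fatigue.
- **The second tester.** A reader might infer that the second researcher is unblinded, or is the AEP. No passage says so. The article condenses a full protocol that is not shown, and that protocol may state the second tester's status.
- **The analyst.** The principal investigator also analyses the data, and enjoyment scores and session adherence exist only for the exercise arm in the first 12 weeks. A reader might infer that these files reveal the group codes before the efficacy comparison. Nothing says when the investigator receives them, and the order of data release is ordinary analysis-plan content. This is not a finding.
- **Disclosure by participants.** Participants know their arm and could mention it to the tester whatever the AEP does. The fix removes one avoidable route, not every route.

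The reply does not answer the central point: the article assigns the task at the testing session itself and states no separation.

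**Conclusion.** The point holds in a limited form. Sections 2.4 and 3.3.3 do not fit together, and the assessor blind is unprotected at tests from 3 months onward. Up to 60 participants, or about 45 after the planned dropout, are tested at the 3-month visit under this arrangement. The outcomes at risk are the five tester-run, effort-dependent secondary measures. The trial's primary conclusion does not rest on this.

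The documents give no figure for observer bias, so its size cannot be stated. That it would favour exercise is plausible but not shown. The verdict assumes that recording at a testing session brings the AEP into contact with the participant or the tester around that visit. If the full protocol already separates them, only the article's wording needs correcting. The change is worth making because it is cheap and because the single-blind description depends on it.

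**What to change.** - **Section 3.3.3.** At post-baseline testing sessions, the blinded tester records only events that occur during the test. The AEP collects all other events away from the session, for example by telephone, on a form the testers do not see.
- **Sections 2.4 and 3.** Reconcile the single investigator who conducts all testing with the two researchers who complete it. State that both testers are blinded and that neither is a trial AEP.

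The cost is revised wording and a separate event form. The small downside is that the AEP's event query moves off the test visit. Exercise participants are already asked at supervised sessions in the first three months, and the AEP telephones every two weeks in the following three. The article describes no such contact for waitlist participants before their 3-month test, or for anyone in the last six months, so a call around those visits would be extra AEP time.
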